#### Missing data

Missing data will be imputed with the last observation-carried forward principle.

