### Interventions

The ambroxol capsules of 600 mg were produced exclusively for this study by a Dutch pharma company. Patients will be titrated up to ambroxol 1800 mg/day or placebo (one capsule three times a day) in 3 weeks, starting with 600 mg once daily during the first week, with weekly increases of 600 mg/day. The dosages of the individual subjects will be decreased if serious side effects occur that are probably related to the treatment.

At 48 weeks, all patients stop using either ambroxol or placebo, followed by a 12 week washout period. This washout period ensures the absence of any symptomatic effect of ambroxol.

At 60 weeks, all baseline measurements will be repeated. Participants will continue their regular medication regimen during the study. Dose adaptations of their standard regimens will be allowed, and will be analyzed post-hoc.

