### Outcomes

The primary endpoint of this study is the change in the MDS-UPDRS part III motor subscale in the practically defined OFF medication state between baseline and 60 weeks. The MDS-UPDRS part III is a motor scale using a score range from 0 to 132 points, with 0 indicating no disability and 132 indicating total disability. All 18 items are evaluated on a five-point scale from 0 to 4. All items contain clearly formulated instructions for both the patient and the investigator [46, 48]. MDS-UPDRS part III in OFF medication state will be assessed every 12 weeks. OFF medication state is defined as withdrawal from dopaminergic medication for at least 8 hours. To ensure the reliability of the UPDRS III scores, several measures were implemented. First, all examiners had to pass the formal MDS-UPDRS training. All MDS-UPDRS III assessments are video recorded and scored by or together with the main co-investigator.

The study has several secondary endpoints, which are also comparing data at 60 weeks versus baseline scores. The following secondary endpoints will be assessed during this study.

*[*
^*18*^
*F]F-DOPA PET*

The PET tracer [^18^F]F-DOPA PET binds to aromatic amino acid decarboxylase (AADC) and estimates the rate of decarboxylation of [^18^F]F-DOPA to [^18^F]fluorodopamine which corresponds to striatal dopamine production and is considered a reliable tool to assess nigrostriatal dopamine synthesis capacity in vivo [49]. The PET-scan is performed after at least 6 hours of fasting (4 hours for diabetic patients). Participants are premedicated with carbidopa, 60 minutes before receiving 200 MBq of the F-DOPA tracer. The F-DOPA PET scan is performed 90 minutes after injection of the tracer on a Siemens HR+ camera. [^18^F]F-DOPA PET will be performed at baseline and at 60 weeks, to analyze the change in striatal activity. [^18^F]FDOPA striatal-to-occipital ratios of the putamen and caudate nucleus will be calculated to quantify the striatal dopaminergic innervation.

*MRI*

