**Fig. 2 Fig2:**
[figure not shown]
Schematic overview of SL metabolism

*Montreal cognitive assessment (MoCA)*

Cognitive impairment is a common non-motor symptom in PD and is an important determinant of functional outcome and quality of life. It affects approximately one in four non-demented PD patients [56, 57]. After a 10-year survival, at least 75% of PD patients will develop Parkinson’s disease dementia (PDD) [58]. The cognitive profile of PD is heterogeneous, but impaired executive functioning is the most prominent symptom [59]. The MoCA is widely used as a global assessment of cognitive function. Therefore, it will be assessed in the ON state at baseline and at 60 weeks.

*The non-motor symptoms scale (NMSS)*

The NMSS is a validated 30-item scale to quantitate various non-motor symptoms of PD. All items are rated both in severity (0–3 points, indicating “none”, “mild”, “moderate” and “severe”, respectively) and frequency (1–4 points, indicating “rarely”, “often”, “frequent” and “very frequent”, respectively) with the eventual score per item being the product of those numbers. This adds up to a final score of 0–360 points, with 0 points indicating no experience of symptoms and 360 points indicating maximum experience of symptoms. The NMSS can be used in all stages of disease progression [60]. The NMSS will be assessed in the ON state at baseline and at 60 weeks.

*Parkinson’s disease questionnaire (PDQ-39)*

The PDQ-39 is a 39-item questionnaire to assess the quality of life of PD patients and consists of 8 domains: mobility, activities of daily of living, emotional well-being, stigma, social support, cognition, communication, and bodily discomfort [61]. All items are rated based on a five-point scale (never, occasionally, sometimes, often, always), scoring 0–4 points, respectively. The total score is calculated by adding up all points scored per item. PDQ-39 will be assessed in the ON state at baseline and at 60 weeks.

*Safety*

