#### Sample size and power calculation

The primary endpoint of this study is the difference in the MDS-UPDRS part III score between the practically defined OFF-state at baseline and 60 weeks, of the ambroxol treated group versus placebo. A previous study with 17 moderate PD patients, treated with high dosages of ambroxol, found an improvement of 6.8 (SD 7.1) points on the MDS-UPDRSIII after 186 days of treatment. However, this was in an open-label non-controlled setting [39].

Ambroxol has never been used for this indication in a double-blind placebo-controlled setting, so insufficient information is available to make a sample size calculation. The effect size was therefore based on collected data about natural disease progression of GBA-PD subjects. Enriching a clinical trial with subgroups of patients, predicted to progress faster on the primary outcome, will considerably reduce the trial size [62]. Several studies calculated the motor progression of GBA-PD. Firstly, GBA-PD patients compared to non-GBA-PD showed a 69% higher decline per year in GBA mutants [62]. Another study reported similar results, with a mean change in the MDS-UPDRS III score per year of 3.4 points (SD 7.7) in GBA carriers. Extrapolating these data to 60 weeks, we postulate an expected difference in MDS-UPDRS-III score of 3.91 points between baseline and 60 weeks in the placebo group. If we would assume no change in MDS-UPDRS III between baseline and 60 weeks in the ambroxol group, a sample size of 80 patients would be required, taking into account a two-sided 5% significance level and a common SD of 6.1, with a power of at least 80% to detect this difference in change of the MDS-UPDRS III score between patients receiving ambroxol and placebo.

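### Carrying the last observation forward does not fit a progressive disease with a post-washout week-60 endpoint, and the direction of the resulting error cannot be predicted

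*Protocol article*

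**What the plan says.** The section Missing data of the protocol article is a single sentence: "Missing data will be imputed with the last observation-carried forward principle". It makes no distinction between outcomes, visits or reasons for missingness.

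The rule has to work with this design:

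- **Endpoint.** Outcomes: "The primary endpoint of this study is the change in the MDS-UPDRS part III motor subscale in the practically defined OFF medication state", taken between baseline and week 60.
- **Visits.** Outcomes: "MDS-UPDRS part III in OFF medication state will be assessed every 12 weeks".
- **Treatment end.** Interventions: "At 48 weeks, all patients stop using either ambroxol or placebo, followed by a 12 week washout period".
- **Purpose of the washout.** Interventions: "This washout period ensures the absence of any symptomatic effect of ambroxol". Trial design and Discussion give the same reason, and Trial design calls such an effect unlikely.
- **Progression.** Sample size and power calculation: "we postulate an expected difference in MDS-UPDRS-III score of 3.91 points between baseline and 60 weeks in the placebo group", with no change assumed on ambroxol.
- **Analysis set.** Statistical analyses admits every patient with at least one follow-up visit, so one early score is enough to enter the primary ANCOVA.
- **Outcomes measured twice.** The F-DOPA PET "will be performed at baseline and at 60 weeks, to analyze the change in striatal activity". For the MoCA: "Therefore, it will be assessed in the ON state at baseline and at 60 weeks". MRI, NMSS and PDQ-39 follow the same two-visit schedule.

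**The concern.** Last observation carried forward (LOCF) assumes that a patient's score would have stayed where it was last seen. That conflicts with this trial in three ways.

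1. The sample size rests on patients getting worse over time. An earlier score understates where a progressing patient would be at week 60.
2. The last scheduled score before week 60 is at week 48, the end of treatment. Anyone on ambroxol who attends week 48 and misses week 60, or who leaves earlier while still on drug, supplies an on-treatment score to an outcome that is meant to be free of symptomatic effect. The imputation then undoes, for those patients, the feature on which a claim of disease modification rests.
3. For outcomes measured only at baseline and week 60, the only value to carry is the baseline one, which scores the patient as unchanged. If that is not intended, the rule is undefined for these outcomes.

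At stake is the primary estimate itself: a real effect may be diluted, or a symptomatic effect may be counted as slowed progression.

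**Working it through.** **Inputs from the protocol article.** Placebo change 3.91 points over 60 weeks; ambroxol change 0 under the alternative; common SD 6.1; two-sided alpha 0.05; 80 patients; visits every 12 weeks; an open-label improvement of 6.8 points in the cited earlier ambroxol study.

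**Assumptions.** 1:1 allocation (40 per arm); linear progression; drop-out rates (none is given); last visit equally likely at week 12, 24, 36 or 48; patients who leave are on drug at their last visit.

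**Step 1: reproduce the plan.**
- 3.4 points per year × 1.15 = 3.91.
- Standard error = 6.1 × √(2/40) = 1.364.
- Power = Φ(3.91/1.364 − 1.96) = Φ(0.907) = 0.818. With the t distribution, 40 per arm gives 0.808 and 39 gives 0.798. The total of 80 reproduces.

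**Step 2: progression lost per patient.** Credited change = 3.91 × week/60.

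| Last visit (week) | Credited | Lost |
|---|---|---|
| 12 | 0.78 | 3.13 |
| 24 | 1.56 | 2.35 |
| 36 | 2.35 | 1.56 |
| 48 | 3.13 | 0.78 |

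The mean loss is 1.955 points.

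**Step 3: the protocol's own alternative, equal drop-out p.** Ambroxol patients do not change, so only placebo drop-outs lose progression. Difference = 3.91 − p × 1.955.
- p = 10%: 3.71, power about 0.78.
- p = 20%: 3.52, power about 0.73.
- p = 30%: 3.32, power about 0.68.

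Simulations of the baseline-adjusted analysis (random slopes, SD of 60-week change 6.1) give 0.75 to 0.76 at 20%. They are slightly higher than the formula because early scores vary less under random slopes.

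**Step 4: no disease modification.** Both arms progress by 3.91. With on-drug symptomatic effect S and drop-out pA (ambroxol) and pP (placebo):

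spurious benefit = pA × S + (pA − pP) × 1.955.

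For pA = 20% and pP = 10%:

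| S | Benefit | Type I error, normal approximation | Type I error, simulation |
|---|---|---|---|
| 0 | 0 + 0.196 = 0.20 | 5.2% | 5-6% |
| 2 | 0.40 + 0.196 = 0.60 | 7.2% | 7-8% |
| 4 | 0.80 + 0.196 = 1.00 | 11.3% | 11% |
| 6.8 | 1.36 + 0.196 = 1.56 | 20.7% | 18-19% |

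At large S the simulation is lower because a mixture of on-drug and washed-out scores widens the spread within the ambroxol arm.

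Unequal drop-out is not required. With 15% in both arms and S = 6.8, the spurious benefit is 0.15 × 6.8 = 1.02 points (26% of 3.91), with a type I error of about 11% by simulation.

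**Step 5: lost progression alone.** With S = 0 and equal drop-out the bias under the null is zero. With 30% versus 10% it is 0.20 × 1.955 = 0.39 points and the type I error is about 6%. The serious inflation comes from carried on-treatment scores.

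**The case against.** The strongest defence is that the damage depends on quantities the documents do not supply. No drop-out rate is given. The protocol regards a symptomatic effect as unlikely, and the sample size section itself warns that the 6.8-point improvement was open-label and uncontrolled. Without a symptomatic effect, type I error hardly moves. All of that stands: 6.8 is an upper bound, and the table has to be read as a range.

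Four stronger readings are tempting, and the documents do not support them.

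- *LOCF favours ambroxol.* Under the protocol's own alternative it works against ambroxol (Step 3). Nor do the documents show that ambroxol patients will drop out more; Background and Discussion describe the drug as well tolerated.
- *Every score before week 60 is on drug.* This is untrue of placebo patients and of those who stop early but keep attending. Unblinding foresees follow-up after discontinuation.
- *Baseline carried forward reproduces the hypothesised ambroxol result on the secondary outcomes.* Zero change is assumed only for MDS-UPDRS III. With equal drop-out, zero change in both arms dilutes an effect and does not create one.
- *No other method exists.* A statistical analysis plan that is not shown may add sensitivity analyses.

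The last point does not remove the problem. The article states a rule. An analysis plan that follows it inherits the defect, and one that departs from it contradicts the published protocol.

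**Conclusion.** The concern holds, with the direction left open. LOCF as the stated rule does not target the washed-out week-60 score that the trial defines as its endpoint, and it cannot be defended as conservative.

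With 20% drop-out in both arms, a true 3.91-point difference is diluted to about 3.5 and power falls to 73-76%. With no true disease modification and 20% versus 10% drop-out, the spurious benefit is about 0.2 points if ambroxol has no symptomatic effect and about 1.6 points at the upper bound of 6.8, with type I error from about 5-6% to 18-21%. These figures rest on the assumed drop-out rates, linear progression and evenly spread last visits. The mismatch between the rule and the endpoint does not depend on them.

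This should be corrected before unblinding, because it acts directly on the primary result.

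**What to change.** Replace LOCF as the main missing-data method.

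- **Primary outcome.** Fit a likelihood-based repeated-measures model to the 12-weekly OFF scores, with treatment-by-visit, baseline-by-visit and the stratification factors, and take the week-60 contrast as the primary test. The week-48-to-60 change is then estimated by arm and not set to zero. Equivalent multiple imputation is acceptable if on-treatment scores do not stand in for washed-out ones.
- **Outcomes measured only twice.** Use multiple imputation for PET, MRI, MoCA, NMSS and PDQ-39.
- **Sensitivity.** Add a delta-adjusted or reference-based analysis, because the main model assumes missing at random. That assumption may not suit patients who leave treatment early. LOCF may stay as a sensitivity analysis only.

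The cost is revised wording, a little more programming and reliance on missing at random. No extra visits or patients are needed.

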### Ethics and dissemination

The GRoningen Early-PD Ambroxol Treatment (GREAT) trial is performed in accordance with the Declaration of Helsinki. The study has been approved by the Medical Research Ethics Committee of the University Medical Center Groningen (METc UMCG) and is registered under METc 2022/179. The study has been reviewed and approved by the Dutch Central Committee on Research involving Human Subjects (CCMO) as competent authority (BI) and is registered under NL77347.042.22. Additionally, the trial is registered at clinicaltrials.gov and is registered under NCT05830396.

Patients received both written and verbal information on the trial before signing the written informed consent.

## Discussion

This study aims to investigate the disease-modifying properties of high-dose ambroxol in PD patients with a GBA mutation. MDS-UPDRS part III in dopaminergic OFF-state is used as the primary outcome measure to investigate the possible disease-modifying effect of ambroxol. Although not perfect, this still is one of the best clinical tools to monitor disease progression [64, 65], in this trial accompanied by imaging markers as well.

Measuring GCase activity in vivo is also a matter of ongoing debate, including the lack of understanding on the precise role of the sphingolipid metabolism and its relationship to PD progression. Our current approach has implemented the most recent findings on sphingolipid metabolism in PD-GBA mutants, using PBMCs (monocytes) and serum sampling [33, 54]. Our sampling strategy represents the major metabolic routes of SLs.

Also, safety and tolerability monitoring are important outcome measures of this study. Side-effects are closely monitored, with extra visits during the titration phase. This allows the investigators to take action on short notice. However, based on previous research, ambroxol has not shown significant safety issues [39, 41, 42].

All PD patients that carry a GBA mutation are allowed in this study. This means that severe, mild and risk variants are included, as well as variants of unknown significance. Based on previous research, it is to be expected that the majority of subjects will be carrier of a risk variant [10]. A post-hoc analysis will be carried out to analyze the effect of ambroxol focused on pathogenic mutations specifically.

Our study uses a washout design, including a 12-week washout period, to eliminate any symptomatic effect of ambroxol.

This trial makes use of capsules, containing 600 mg of ambroxol, which will improve the tolerability and compliance of this treatment.

This is a single-center study, which will improve the homogeneity of the study population. The nation-wide screening in the Netherlands, now complemented with an additional population-wide screening, has resulted in large numbers of PD patients with a known GBA status. There will be an overrepresentation of participants from the northern part of the Netherlands, because the additional screening will take place especially in the neurology practices in the northern counties of the Netherlands.

The intention of this trial is to demonstrate the possible disease-modifying properties of ambroxol. We will have to wait for the trial data, however, in order to see whether these expectations were too optimistic.

## Data Availability

No datasets were generated or analysed during the current study.

## Abbreviations

AADC: Aromatic amino acid decarboxylase
AE: Adverse event
aSyn: Alpha-synuclein
BI: Competent authority; in Dutch: Bevoegde Instantie
CCMO: Dutch central committee on research involving human subjects; in Dutch: centrale commissie mensgebonden onderzoek
CSF: Cerebrospinal fluid
DBS: Deep brain stimulator
DSMB: Data safety monitoring board
DTI: Diffusion tensor imaging
DUPARC: Dutch Parkinson Cohort study
ECG: Electrocardiogram
eCRF: electronic case report form
ER: Endoplasmic reticulum
[^18^F]F-DOPA: 6-[18F]-fluoro-L-3,4-dihydroxyphenylalanine
GBA-PD: Parkinson patients carrying a *GBA1* mutation
GCase: Glucocerebrosidase
GD: Gaucher disease
GluCer: Glucosylceramide
GREAT: GRoningen early-PD ambroxol treatment
LED: Levodopa equivalent dose
MDS: Movement Disorder Society
METC: Medical research ethics committee (MREC); in Dutch: medisch-ethische toetsingscommissie
MIC: Mild cognitive impairment
MOCA: Montreal cognitive assessment
MRI: Magnetic resonance imaging
NMSS: Non-motor symptoms scale
PBMCs: Peripheral mononuclear blood cells
PD: Parkinson’s disease
PDD: Parkinson’s disease dementia
PDQ-39: 39 item Parkinson’s disease questionnaire
PET: Positron emission tomography
PFD-FDGlu: 5-(Pentafluorobenzoylamino) Fluorescein di-beta-D-glucopyranoside
PI: Principal investigator
PPNN: Parkinson platform Noord Nederland
QoL: Quality of life
(S)AE: (Serious) Adverse event
SL: Sphingolipid
Sponsor: The sponsor is the party that commissions the organisation or performance of the research, for example a pharmaceutical, company, academic hospital, scientific organisation or investigator. A party that provides funding for a study but does not commission it is not regarded as the sponsor, but referred to as a subsidising party
UMCG: University Medical Center Groningen; in Dutch: Universitair Medisch Centrum Groningen
UPDRS: MDS unified parkinson’s disease rating scale
